## (IV) Termination Criteria

Patients should terminate the study treatment in any of the following cases:

1. Disease progression determined by investigator;
2. Occurrence of intolerable toxicity;
3. Treatment is delayed 14 days or more due to adverse reaction or other reasons;
4. Patient’s compliance is poor;
5. The investigator believes that patient is not suitable for continuing such treatment or the patient cannot benefit from the treatment;
6. Subject requests withdrawal.

Once a subject withdraws from the study, the investigator must record the reason for withdrawal in his/her case report form or medical record. All subjects who withdraw from the study due to adverse event or clinical laboratory abnormality must be followed up until recovered or stable, with their subsequent outcome recorded.

# V. Clinical Study Assessments

## (I) Screening/Baseline Measurements

| Assessment Items | | Time Prior to First Dose |
| --- | --- | --- |
| 1. ICF | Signing | Prior to first dose |
| 2. Medical history and physical examination | Medical history: Diagnosis of ESCC, concomitant medications, history of hypersensitivity to the investigational drug, and general past medical history, including concomitant diseases.  Physical examination: Body height, body weight, ECOG performance status score (see Annex 1 for details), current symptoms, nervous system examination. | 14 days |
| 3. Routine blood test | Hemoglobin, platelet, white blood cell, neutrophil | 7 days |
| 4. Biochemistry | Serum biochemistry (ALT, AST, AKP, BIL, BUN, Crea, ALB, TG, TCHO, CRP, electrolytes) | 14 days |
| 5. Routine urine test | Urine PH, urine protein, urine red blood cell, urine white blood cell | 14 days |
| 6. Imaging* | CT or MRI | 21 days |
| 7. Electrocardiogram | 12-lead ECG | 21 days |
| 8. Pathology | Endoscopic biopsy and pathology | No limit |
| 9.Quality of life evaluation | EORTC QLQ-C30 and EORTC QLQ-OES18 | 3 days |
| * To evaluate the efficacy, pre-treatment and post-treatment CT or MRI scans should be performed by the same methods for comparison. | | |

# VI. Collection and Handling of Clinical Study-related Specimens

During this study, subject’s related samples for routine blood test, serum biochemistry, blood coagulation and routine urine test, etc. will be collected by the investigator and professional personnel in a scientific and standard manner and preserved in the Laboratory Department of Beijing Cancer Hospital. The above test samples will be destructed by the site within 14 days after the test results are confirmed.

# VII. Investigational Drug in the Study

## (I) Name and Strength of Study Medications:

**1. Afatinib Dimaleate (Giotrif)**

**1.1 General information:**

a) Dosage form: Tablets, 40 mg/tablet;

b) Dosage and administration: 40 mg Qd; in case of intolerable adverse drug reaction, the dose will be adjusted to 30 mg Qd or 20 mg Qd. If the patient cannot tolerate 20 mg/day, consider permanent discontinuation of afatinib.

c) Storage condition: Store in a tightly closed container.

**1.2 Instructions for use:**

a) Afatinib should not be taken with meal. Take afatinib at least 3 hours after or 1 hour before a meal and swallow the tablet as whole with water;

b) Dose reduction can decrease the incidence of common adverse reactions;

c) Adequate contraception should be taken during the treatment period and until at least 2 weeks after the last dose;

**1.3 Adverse reactions:**

a) Gastrointestinal reactions: Diarrhea has resulted in drug withdrawal in about 2% of patients. Diarrhea usually occur within the first 2 weeks of treatment and may result in dehydration with or without renal impairment. Therefore, anti-diarrheal medicinal products (e.g., Loperamide) should be used at first signs of diarrhea. Patients with severe diarrhea (grade 2 or 3 diarrhea persisting more than 48 hours) may require interruption and dose reduction or discontinuation of therapy with afatinib.

b) Skin related adverse events: Rash/ache has resulted in drug withdrawal in about 2% of patients and generally manifests as a mild or moderate erythematous and acneiform rash, which may occur or worsen in areas exposed to sun. For patients who are exposed to sun, protective clothing, and/or use of sun screen is advisable. Early intervention (such as emollients, antibiotics) of dermatologic reactions is recommended. For patients with severe bullous, blistering or exfoliative sin conditions, discontinue afatinib therapy permanently and refer to a specialist with expertise in managing these dermatologic effects.

c) Interstitial lung disease: Interstitial lung disease (ILD) or ILD-like adverse reactions (e.g., lung infiltration, pneumonitis, acute respiratory distress syndrome or allergic alveolitis) are reported in 1.6% of patients treated with afatinib, and 0.4% of them die. Interrupt afatinib therapy in all patients with acute onset and/or unexplained worsening of pulmonary symptoms (dyspnea, cough, fever). If ILD is diagnosed, discontinue afatinib permanently and refer to a respiratory specialist in managing the condition.

d) Hepatic function: Hepatic failure has been reported during treatment with afatinib in 1% of patients. Periodic liver function testing is recommended.

e) Keratitis: Symptoms such as acute or worsening eye inflammation, lacrimation, light sensitivity, blurred vision, eye pain and/or red eye should be referred promptly to an ophthalmology specialist. If a diagnosis of ulcerative keratitis is confirmed, treatment should be interrupted.

**1.4 Contraindications:**

Contraindicated in patients with known hypersensitivity to afatinib or to any of the excipients.

**1.5 Drug interactions:**

a) Concomitant taking of strong P-glycoprotein (p-gp) inhibitors (e.g., cyclosporine A, ketoconazole, itraconazole, erythromycin, verapamil, quinidine, tacrolimus, amiodarone, etc.) with afatinib can increase exposure to afatinib;

b) Concomitant taking of strong p-gp inducers (e.g., rifampicin, carbamazepine, phenytoin, phenobarbital, or St. John’s wort) with afatinib can decrease exposure to afatinib;

**1.6 Food effect on afatinib:**

a) Co-administration of a high-fat meal with afatinib can result in a significant decrease of exposure to afatinib

## (II) Dosage Regimen:

Afatinib (40 mg Po Qd) therapy, 4-week cycles, until disease progression, occurrence of intolerable toxicity, loss to follow-up or death, or other situations in which the investigator determines the treatment should be discontinued.

## (III) Regimen Adjustment

Dose adjustment of afatinib

| CTCAE drug-related adverse events | Recommended dose of afatinib |
| --- | --- |
| Grade 1 or 2 | Do not interrupt the treatment or adjust the dose |
| Grade 2 (prolonged, for example, diarrhea > 48 hour and/or rash > 7 days, or intolerable) or ≥ Grade 3 | Interrupt the treatment until the event is resolved to grade 0/1, and then restore the treatment with the dose reduced by 10 mg. If the patient cannot tolerate 20 mg/day, consider permanent discontinuation of afatinib. |

If a patient’s treatment is delayed due to adverse reaction but there is no explicit evidence of tumor progression, the clinical study can be continued no matter how long the treatment is delayed.

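### The grade-based dose-adjustment table conflicts with the event-specific stop and interrupt rules in section VII (I) 1.3, and the protocol does not say which prevails

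*Protocol*

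**What the plan says.** Section VII (III), Regimen Adjustment, gives a two-row table for drug-related adverse events, sorted by CTCAE grade.

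- **Row 1** covers grade 1 or 2: "Do not interrupt the treatment or adjust the dose".
- **Row 2** covers grade 2 that is prolonged or intolerable, and grade 3 or higher: "Interrupt the treatment until the event is resolved to grade 0/1, and then restore the treatment with the dose reduced by 10 mg". The only mention of a permanent stop is that it should be considered if 20 mg/day is not tolerated.

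Section VII (I) 1.3, Adverse reactions, gives instructions by event.

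- **1.3(b), severe bullous, blistering or exfoliative skin reactions:** "discontinue afatinib therapy permanently and refer to a specialist with expertise in managing these dermatologic effects".
- **1.3(c), lung symptoms:** "Interrupt afatinib therapy in all patients with acute onset and/or unexplained worsening of pulmonary symptoms".
- **1.3(c), ILD:** "If ILD is diagnosed, discontinue afatinib permanently and refer to a respiratory specialist in managing the condition". The same item says that ILD or ILD-like reactions "are reported in 1.6% of patients treated with afatinib, and 0.4% of them die".
- **1.3(e), keratitis:** once ulcerative keratitis is confirmed, treatment is to be interrupted.

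The permanent stop for ILD and both interruption rules carry no grade limit. The Synopsis (Treatment Regimen) and section VII (I) 1.1(b) repeat only the reduction in 10 mg steps, for reactions the patient cannot tolerate, and name no exception.

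**The concern.** The table and section 1.3 give the treating physician different orders for the same patient. Neither refers to the other, and the protocol contains no statement of precedence. The table is the part titled as the rule for adjusting the regimen, so it is where a physician would look for a dosing decision. Section 1.3 reads as drug information.

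At stake is patient safety: afatinib continued during low-grade diagnosed ILD or low-grade ulcerative keratitis, or restarted after ILD or a severe skin reaction. The protocol itself treats ILD as a serious hazard. It reports deaths from it in 1.3(c), and section IV (II), item 13, excludes patients with a history or baseline imaging evidence of it.

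**Working it through.** The plan gives no figure to reproduce, and the point rests on no calculation. The check sets the two sections side by side for each event that 1.3 singles out. Row 1 in effect means grade 1, or grade 2 that is tolerable and not prolonged, because row 2 takes the rest of grade 2.

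| Event, if judged drug-related | Section 1.3 | Table row 1 | Table row 2 |
| --- | --- | --- | --- |
| Diagnosed ILD | Permanent stop, no grade limit | Continue unchanged: **conflict** | Resume 10 mg lower after recovery: **conflict** |
| Severe bullous, blistering or exfoliative skin reaction | Permanent stop | Not normally reached | Resume 10 mg lower after recovery: **conflict** |
| Acute or unexplained worsening of lung symptoms | Interrupt, no grade limit | Continue unchanged: **conflict** | Interrupt: agrees |
| Confirmed ulcerative keratitis | Interrupt, no grade limit | Continue unchanged: **conflict** | Interrupt: agrees |

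Notes on the cells:

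1. **ILD, row 2.** A patient on 40 mg with grade 3 ILD that improves restarts at 40 − 10 = 30 mg under the table and never restarts under 1.3(c). The table counts grade 1 as recovered, so a restart would be allowed with ILD still present at grade 1.
2. **Skin, row 1.** Section 9.1.7 equates severe with grade 3, so an event that is severe by description falls in row 2.
3. **Lung symptoms.** The table applies only to drug-related events. While symptoms remain unexplained they may not yet have been attributed to afatinib, so the conflict arises once they are recorded as drug-related.
4. **No recovery.** If an event in row 2 never returns to grade 0/1, the table does not restart afatinib either, and the two sections agree in effect.

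Next, whether anything else in the protocol settles the matter. Section IV (IV), Termination Criteria, has three relevant items:

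- Item 2, intolerable toxicity, does not reach a tolerable low-grade event.
- Item 3, a delay of 14 days or more, does not apply to a patient who is never interrupted and does not prevent a restart before day 14.
- Item 5, the investigator's judgement, permits a stop but does not require one.

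None names ILD or the skin reactions. These items narrow the conflict without removing it.

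**The case against.** The strongest reply is that the protocol already contains the right instruction. Section 1.3 sits in the same chapter, is specific and imperative, and by ordinary reading a specific mandatory stop overrides a general ladder whose column is headed as a recommended dose. To continue through ILD, or to restart after a severe skin reaction, a physician would have to set aside plain text. Eligibility also removes patients with known ILD, and the termination criteria always allow a stop. Much of this stands: 1.3 is the likely intended rule, and most physicians would probably follow it. But that is an inference. The rows of the table are worded as directions, and what they direct is what 1.3 forbids.

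Three stronger readings are tempting, and the documents do not support them.

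- **A reader might turn the 1.6% rate into a risk of mismanagement.** With 40 patients the expected number of ILD or ILD-like reactions would be 40 × 0.016 = 0.64. That counts events, not wrong decisions. A wrong decision also needs the event to be drug-related, diagnosed as ILD, low grade or recovering, and 1.3 to be disregarded. The protocol gives no figure for these steps and no rate for this population.
- **A reader might add the contradiction over treatment delays.** The last sentence of Regimen Adjustment says that "the clinical study can be continued no matter how long the treatment is delayed", against the 14-day limit in Termination Criteria item 3. It touches every toxicity and is a separate issue, so it adds no weight here.
- **A reader might infer that the Synopsis and section 1.1(b) also tell sites to continue through low-grade ILD.** They do not. They cover only reactions the patient cannot tolerate.

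**Conclusion.** The inconsistency is real. The table conflicts with 1.3 in four situations: two where 1.3 requires a permanent stop, and two where it requires interruption and row 1 says to carry on. Confidence in the textual conflict is high. How often it would change care cannot be estimated from the documents, and section 1.3 is probably how the protocol would be applied.

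This is a patient-safety consistency error, not a flaw in the statistical design. The two-stage boundaries, the sample size of 40 and the analysis of objective response rate are unaffected. It should be corrected because a stated rule, followed as written, produces an action that another stated rule forbids, for a toxicity that the protocol reports as sometimes fatal. The conclusion assumes only that the events concerned are judged drug-related, which is what brings them under the table.

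**What to change.** Add one line directly under the table, for example: *Exceptions regardless of grade: interrupt afatinib for acute or unexplained worsening of pulmonary symptoms and for confirmed ulcerative keratitis; discontinue it permanently, without resumption, for diagnosed ILD and for severe bullous, blistering or exfoliative skin conditions.*

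Cross-refer to this line from the Synopsis (Treatment Regimen) and from section VII (I) 1.1(b). List the two permanent-stop events as reasons in section IV (IV), Termination Criteria.

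Keep the exception to these named events. A general statement that 1.3 overrides the table would weaken the diarrhoea rule. The table requires interruption for grade 2 diarrhoea beyond 48 hours and for grade 3, whereas 1.3(a) says only that such patients "may require interruption and dose reduction or discontinuation of therapy with afatinib".

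The cost is a minor text amendment and a notice to the site. Sample size and analysis do not change.

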## (IV) Concomitant Medications

**1. Permitted Medications**

For the treatment of pain, infections and other tumor complications and/or study treatment-related toxicities during the study, sedatives, antibiotics, analgesics, antihistamines, steroids, granulocyte colony-stimulating factor and transfusion of red blood cells, platelets or fresh frozen plasma may be administered.

**2. Prohibited Medications**

During the study, subjects are not allowed to use Chinese medicines with an antitumor effect indicated in the package insert; and not allowed to receive concomitant, long-term systemic immunotherapy, chemotherapy, radiotherapy (except palliative radiotherapy), hormonal therapy for treatment of tumors (however, glucocorticoids for antiemetic purpose and progestogen for tumor cachexia are exceptions), or other investigational drugs.

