# Synopsis of the Study Protocol

| Study Title | A Phase II Clinical Study to Evaluate the Efficacy and Safety of Afatinib for Pretreated Patients with Advanced Esophageal Squamous Cell Carcinoma with EGFR Overexpression/Amplification |
| --- | --- |
| Study Objective | To explore the efficacy and safety of afatinib as the second-line or beyond therapy for advanced esophageal squamous cell carcinoma (ESCC) with EGFR overexpression/amplification |
| Trial Site | Peking University Cancer Hospital and Institute |
| Trial Design | A non-randomized, open-label, single-arm clinical study. Subjects receive afatinib (40 mg po. Qd) in 4-week cycles until disease progression, occurrence of intolerable toxicity, loss to follow-up or death, or other situations in which the investigator determines the treatment should be discontinued. |
| Number of Subjects | 40 |
| Study Endpoints | Primary study endpoint: Objective response rate (ORR)  Secondary study endpoints: Disease control rate (DCR), safety, progression Free Survival (PFS) and overall survival (OS)  Exploratory endpoint: Quality of life, efficacy markers |
| Study Duration | First Patient In Time (FPI): 05/2019  Last Patient In Time (LPI): 05/2020 |
| Inclusion Criteria | 1. Voluntarily participating and signing the Informed Consent Form; 2. Age: 18 to 70 years of age; 3. Male or female; 4. Pathologically confirmed ESCC; 5. Pathologically confirmed immunohistochemical EGFR (3+) or EGFR-FISH amplification or EGFR amplification by NGS-testing (see Annex 4 for specific testing standards) 6. Radiographically confirmed unresectable advanced ESCC; 7. Failure of the first-line or beyond therapy; 8. At least one measurable lesion (per RECIST 1.1 criteria), with the imaging diagnosis ≤ 21 days apart from the enrollment time; 9. Life expectancy of ≥ 3 months; 10. General performance status (ECOG) score of 0-2; 11. Sufficient bone marrow hematopoiesis (within 7 days): hemoglobin ≥ 9 g/dL, white blood cell ≥ 3.0 × 10^9^/L, neutrophil ≥ 1.5 × 10^9^/L, platelet ≥ 100 × 10^9^/L; normal hepatic and renal functions (within 14 days): TBIL ≤ 1.5 × upper limit of normal (ULN); ALT and AST ≤ 2.5 × ULN, or ≤ 5 × ULN in the presence of liver metastasis; creatinine ≤ 1.5 × ULN; 12. Cardiac, pulmonary, renal and hepatic functions are basically normal; |

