## (II) Exclusion Criteria

1. Patients who are currently receiving other effective treatment regimens;
2. Participation in other clinical trials within 4 weeks prior to enrollment;
3. Inability to cooperate in oral administration of afatinib;
4. No measurable tumor lesion, for example, body cavity fluid or diffuse organ infiltration;
5. Prior radiotherapy on the measurable lesion;
6. Prior use of anti-EGFR targeted therapy;
7. Coexistence of other primary malignancies other than esophageal cancer, excluding cured basal cell carcinoma of skin and cervical carcinoma in situ;
8. Clinically significant cardiovascular diseases such as heart failure (NYHA class III-IV), uncontrolled coronary heart disease, cardiomyopathy, arrhythmia, uncontrolled hypertension, or history of myocardial infarction within the past 1 year;
9. Nervous or mental disorders affecting the cognitive ability, including central nervous system metastasis;
10. Severe active clinical infection (at grade >2 per NCI-CTCAE Version 4.0) including active tuberculosis within 14 days prior to enrollment;
11. Known or self-complained HIV infection or active hepatitis B or hepatitis C;
12. Uncontrolled systemic diseases such as poorly uncontrolled diabetes mellitus;
13. History of interstitial lung disease such as interstitial pneumonia and pulmonary fibrosis, or chest X-ray/CT evidence of interstitial lung disease at baseline;
14. Keratitis, ulcerative keratitis or severe xerophthalmia;
15. Known hypersensitivity or allergic reaction to any component of the investigational drug;
16. Pregnancy (confirmed by serum β-chorionic gonadotrophin test) or lactation;

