## (III) Removal Criteria

1. Non-compliance with inclusion criteria;
2. Patients who violate the requirements of the study protocol, fail to take medicines as required and fail to complete the plan;
3. Poor quality of data recording, and incomplete and inaccurate data.
4. Use of other antitumor drug therapy during the clinical study period.

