| Partial response (PR): | At least a 30% decrease in the sum of the LD of target lesions, taking as reference the baseline sum LD. |
| Progressive disease (PD): | At least a 20% increase in the sum of the LD of target lesions, taking as reference the smallest sum LD recorded since the treatment started or the appearance of one or more new lesions. |
| Stable disease (SD): | Neither sufficient shrinkage to qualify for PR nor sufficient increase to qualify for PD, taking as reference the smallest sum LD since the treatment started. |

Evaluation of non-target lesions

| Complete response (CR): | Disappearance of all non-target lesions and normalization of tumor marker level. |
| --- | --- |
| Incomplete response or stable disease (SD): | Persistence of one or more non-target lesion(s) or/and maintenance of tumor marker level above the normal limits. |
| Progressive disease (PD): | Appearance of one or more new lesions and/or unequivocal progression of existing non-target lesions. Although an unequivocal progression of existing “non-target” lesions is exceptional, in such circumstances, the opinion of the treating physician should prevail and the progression status should be confirmed later on by the review panel (or study chair). |

Evaluation of best overall response

The best overall response is the best response recorded from the start of the treatment until disease progression/recurrence (taking as reference for PD the smallest measurements recorded since the treatment started). In general, the patient’s best response assignment will depend on the achievement of both measurement and confirmation criteria.

| Target lesions | Non-target lesions | New lesions | Overall response |
| --- | --- | --- | --- |
| CR | CR | No | CR |
| CR | Non-CR/SD | No | PR |
| PR | Non-PD | No | PR |
| SD | Non-PD | No | SD |
| PD | Any | Yes or No | PD |
| Any | PD | Yes or No | PD |
| Any | Any | Yes | PD |

- Patients with a global deterioration of health status requiring discontinuation of treatment without objective evidence of disease progression at that time should be classified as having “symptomatic deterioration”. Every effort should be made to document the objective progression even after discontinuation of treatment.

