- In some circumstances it may be difficult to distinguish residual disease from normal tissue. When the evaluation of complete response depends on this determination, it is recommended that the residual lesion be investigated (fine needle aspirate/biopsy) to confirm the complete response status.
- Confirmation.
- The main goal of confirmation of objective response is to avoid overestimating the response rate observed. In cases where confirmation of response is not feasible, it should be made clear when reporting the outcome of such studies that the responses are not confirmed.
- To be assigned a status of PR or CR, changes in tumor measurements must be confirmed by repeat assessments that should be performed no less than 4 weeks after the criteria for response are first met. Longer intervals as determined by the study protocol may also be appropriate.
- In the case of SD, follow-up measurements must have met the SD criteria at least once after study entry at a minimum interval (in general, not less than 6-8 weeks) that is defined in the study protocol.
- Duration of overall response.
- The duration of overall response is measured from the time measurement criteria are met for CR or PR (whichever status is recorded first) until the first date that recurrence or PD is objectively documented, taking as reference for PD the smallest measurements recorded since the treatment started.
- Duration of stable disease
- SD is measured from the start of the treatment until the criteria for disease progression are met, taking as reference the smallest measurements recorded since the treatment started.
- The clinical relevance of the duration of SD varies for different tumor types and grades. Therefore, it is highly recommended that the protocol specifies the minimal time interval required between two measurements for determination of SD. This time interval should take into account the expected clinical benefit that such a status may bring to the population under study.
- Response review.
- For clinical trials where the response rate is the primary endpoint it is strongly recommended that all responses be reviewed by an expert(s) independent of the study at the study’s completion. Simultaneous review of the patients’ files and radiological images is the best approach.
- Reporting of results.

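### Palliative radiotherapy is permitted on study with no rule for scoring an irradiated target lesion, so radiation shrinkage could count as a response in the primary ORR

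*Protocol*

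**What the plan says.** Four parts of the protocol bear on this.

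- **On-study treatment.** The Prohibited Medications section (VII, Concomitant Medications) bans "radiotherapy (except palliative radiotherapy), hormonal therapy for treatment of tumors" and several other treatments. The palliative exception says nothing about which lesion may be irradiated.
- **Entry.** Item 5 of the exclusion criteria, in both the Synopsis and section IV, is "Prior radiotherapy on the measurable lesion".
- **Removal and termination.** The fourth removal criterion is "Use of other antitumor drug therapy during the clinical study period", which covers drugs and does not name radiotherapy. The termination criteria do not mention radiotherapy either.
- **Response scoring.** ORR (CR+PR) is the primary endpoint. Annex 2 defines PR as "At least a 30% decrease in the sum of the LD of target lesions, taking as reference the baseline sum LD". It also states: "The best overall response is the best response recorded from the start of the treatment until disease progression/recurrence". A response "must be confirmed by repeat assessments that should be performed no less than 4 weeks after the criteria for response are first met". Neither Annex 2 nor the Treatment Outcome Measures section says how to score a target lesion irradiated on study.

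**The concern.** The protocol keeps irradiated measurable lesions out at entry but has no matching provision once treatment begins, although irradiation after the baseline scan can change a lesion relative to its reference measurement. Radiation shrinkage that is large enough and lasts until the confirmation scan meets the stated definition of PR. Confirmation shows that the shrinkage persisted; it does not show what caused it.

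The design offers no correction. There is no control arm in which the same misclassification would appear, and the trial is decided on a count of responders among 40 patients. The same gap touches two secondary endpoints: if radiation holds an irradiated target small, progression in that lesion may not show in DCR or PFS.

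**Working it through.** **1. Does any provision discount an irradiated target?**

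| Provision | Effect on a target irradiated on study |
|---|---|
| Exclusion item 5 | None; applies before entry only |
| Removal item 4 | None; other antitumor drugs only |
| Termination criteria | Radiotherapy not listed |
| Annex 2, PR definition | Counts the fall in the sum whatever its cause |
| Annex 2, best overall response | Window closes at progression, not at radiotherapy |
| Confirmation (section V footnote, Annex 2) | Tests persistence, not cause |
| Annex 2, unknown/not assessable category | Available, but nothing assigns irradiated targets to it |

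No provision requires such a response to be discounted.

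**2. Reproducing the design.** Inputs from the Synopsis: p0 = 0.10, p1 = 0.25, α = 0.05, power 0.8, N1 = 22, R1 = 2, N = 40, R2 = 8. The decision rule is not spelled out. Take it as stop at 2 or fewer responses in 22, and success at 8 or more in 40. Then

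P(success | p) = Σ (x = 3 to 22) P[Bin(22, p) = x] × P[Bin(18, p) ≥ 8 − x]

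- p = 0.10: type I error 0.0398 (probability of stopping early 0.620)
- p = 0.25: power 0.803

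This matches the stated α and power. If 8 were instead the last failing count, so that 9 or more were needed, type I error would be 0.015 and power 0.693, short of the stated 0.8. The first reading is therefore the likelier one.

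**3. Illustrating the effect.** Suppose the true ORR is 0.10 and a share q of true non-responders is scored as PR because radiation shrank a target. The apparent rate is

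p* = 0.10 + 0.90q

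and the expected number of false responses among 40 patients is 40 × 0.90 × q = 36q. The protocol gives no q, so the values below are assumptions.

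| q | p* | False responses expected in 40 | Type I error, success at ≥8/40 | Type I error, success at ≥9/40 |
|---|---|---|---|---|
| 0 | 0.100 | 0 | 0.040 | 0.015 |
| 1% | 0.109 | 0.36 | 0.061 | 0.025 |
| 2.5% | 0.1225 | 0.9 | 0.104 | 0.048 |
| 5% | 0.145 | 1.8 | 0.207 | 0.113 |

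One false response adds 1/40 = 2.5 percentage points to the observed ORR, against a design difference of 25 − 10 = 15 points.

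**The case against.** The strongest objection is that evaluability and censoring rules usually sit in a statistical analysis plan, which may exist and is not shown. This stands for PFS and SD after irradiation. It does not dispose of the ORR point: the protocol itself permits the radiotherapy, bars irradiated lesions at entry and fixes an explicit PR rule, and that rule applied as written can give a wrong primary result.

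The entry exclusion and the concomitant-treatment rule do not contradict each other; both can be followed. The protocol also gives no reason for the exclusion, so reading it as protection of the response measurement is an inference. What is missing is a link between the two.

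Several safeguards narrow the exposure. Progression closes the best-response window, so radiotherapy given for a lesion already meeting PD cannot create a later response. The whole target sum, over as many as 10 lesions, must fall by 30% and the fall must be confirmed. Annex 2 strongly recommends independent review of responses where response rate is the primary endpoint, and has a not-assessable category that counts as failure. The on-treatment schedule already collects concomitant therapies every 4 weeks. None of these obliges anyone to discount a response in an irradiated target, and the schedule does not ask which lesion was treated.

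Two stronger readings are tempting. A reader might infer that radiation responses will enter the numerator and that the false-positive rate is in fact doubled or worse. The protocol gives no frequency of palliative radiotherapy, so it supports only that this could happen. A reader might also infer that progression in general is hidden from PFS and DCR. New lesions, unequivocal non-target progression and sufficient growth of the target sum still give PD; only regrowth in the irradiated lesion itself could be masked.

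**Conclusion.** The point holds as a gap in a stated rule. On the protocol's wording, shrinkage of a target lesion irradiated on study could be counted as an afatinib response in the primary ORR, and regrowth in that lesion could be masked for DCR and PFS.

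The size cannot be established from the document. The type I error figures rest on assumed misclassification rates and on an unstated decision rule. At 8 or more in 40, even 1% misclassification takes the error past the stated 0.05. At 9 or more in 40, the error stays just under 0.05 at 2.5% and exceeds it at 5%. They show how little margin the design has and do not predict what will occur.

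**What to change.** Reconcile the exclusion criterion, the Prohibited Medications section and the Annex 2 response criteria by adding a scoring rule to the Treatment Outcome Measures section, for example:

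*Once a target lesion has been irradiated on study, later assessments cannot establish or confirm CR or PR. A patient without a confirmed response before that date remains in the denominator as a non-responder.*

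Record the anatomical site and date of any on-study radiotherapy on the CRF, so that the rule can be applied.

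The rule governs scoring only and does not change whether palliative radiotherapy may be given. Leave PFS and SD after irradiation to the analysis plan. Censoring PFS at the last scan before irradiation is one option, but it may be informative if irradiation follows symptomatic worsening, and it discards progression documented later.

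The cost is two sentences and one CRF item. Reported ORR may be slightly lower. The sample size of 40 and the decision bounds are unaffected.
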